### Outcome assessment

#### Primary endpoint

The primary endpoint for this study will be overall survival (OS), as defined by time elapsed from date of diagnosis to death or last follow up.

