#### Chart abstraction

Clinical information will be abstracted from the patient’s medical record at baseline (at time of study enrollment), during treatment(s), and following completion of any treatment(s). Clinical and treatment data collected through chart abstraction is summarized in Table 3. Treatment data will include dates of treatment, procedural details (stenting, esophagectomy, gastrostomy tube placement), radiation treatment regimens, chemotherapy regimens, major treatment- and disease-related complications, best response to treatment (if evaluated), reasons for discontinuing treatment or pursuing supportive care, and date and cause of death. Data will be collected on the time elapsed from diagnosis to initiation of treatment to account for any treatment delays that may explain differences in survival during analyses.

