OS will be defined in two ways: 1) from the date of initial diagnosis to the date of death or last patient contact; and 2) from date of initiation of treatment to date of death or the date of last patient contact. Kaplan-Meier method will be used to summarize OS and log-rank test will be used to compare survival curves among treatments overall and stratified by the study center. Furthermore, Cox proportional hazards (cph) modeling will be used to account for demographic and clinicopathological factors by including them as covariates. Proportionality of hazards for key covariates will be tested by examining the correlation between time and scaled Schoenfeld residuals and log-log plots of survival. Important covariates that violate the proportionality assumption will be used to stratify the cph model. In many settings in Eastern Africa, long delays can occur between diagnosis and initiation of treatment. To mitigate immortal time bias that can emerge in time-to-event analyses of observational studies, two analytical approaches will be employed. First, in analyses using OS defined by date of diagnosis, the time from diagnosis to the initial treatment will be added as a covariate. Secondly, in analyses of associations between different treatments and OS, treatment status will be included in Cox regression modeling as a time-varying covariate (defined as treated versus untreated). This approach allows for patients to accrue follow up time while awaiting treatment, while also accounting for any events that occur during the ‘untreated’ waiting period [20]. Our primary analysis will examine pairwise comparisons of: stenting vs. radiotherapy with or without chemotherapy, stenting vs. chemotherapy, and radiotherapy with or without chemotherapy vs. chemotherapy. Among patients receiving radiation, outcomes may differ between patients receiving radiotherapy alone as compared to concurrent chemoradiation. Exploratory analyses will examine these subgroups separately.

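### On the diagnosis clock, time to treatment entered as a covariate looks protective by construction; delayed entry at treatment start should replace it in the modality contrasts

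*Protocol article*

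**What the plan says.** The Primary endpoint section fixes overall survival "as defined by time elapsed from date of diagnosis to death or last follow up". The Statistical methods section adds a second definition, "from date of initiation of treatment to date of death or the date of last patient contact". It notes that "long delays can occur between diagnosis and initiation of treatment" and continues: "To mitigate immortal time bias that can emerge in time-to-event analyses of observational studies, two analytical approaches will be employed".

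- First approach: "in analyses using OS defined by date of diagnosis, the time from diagnosis to the initial treatment will be added as a covariate".
- Second approach: "treatment status will be included in Cox regression modeling as a time-varying covariate (defined as treated versus untreated".

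The article calls only the second term time-varying, so the natural reading of the first is a fixed covariate. No delayed entry or landmark is described for that model. On model checking the section says: "Important covariates that violate the proportionality assumption will be used to stratify the cph model". The Chart abstraction section gives the reason for recording the wait, which concerns survival: "Data will be collected on the time elapsed from diagnosis to initiation of treatment to account for any treatment delays that may explain differences". The article gives no distribution of waiting times, either overall or by modality.

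**The concern.** Call the wait W. On the diagnosis clock W is not known at time zero. A patient treated at week 12 has, by definition, lived 12 weeks. In a model with W as a fixed covariate, that patient sits in the risk set for 12 weeks during which death was impossible, and the model attributes the absence of deaths to the size of W. The coefficient is then negative even if delay does nothing.

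The stake is the reading of that coefficient. The article records delay because it may account for survival differences, and time to treatment is one of its process measures. A table from the primary-clock model showing lower mortality with longer waits would be an artefact that points in a harmful direction. A secondary question is whether carrying W in the model costs the modality contrasts any precision.

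**Working it through.** **Inputs from the Sample size section.** Stenting 1102; radiotherapy with or without chemotherapy 464 + 212 = 676; median survival 36 and 27 weeks; alpha 0.0167; stated power 0.99 for this contrast. Under exponential survival the implied hazard ratio is 27/36 = 0.75.

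**The plan's own figure.** Power = Φ(√(d·p(1−p))·|ln HR| − z), with p = 1102/1778 = 0.620, p(1−p) = 0.2356, |ln 0.75| = 0.2877 and z = 2.394 (two-sided, assumed). With d = 1545 events (about what 6 to 53 months of follow-up would give), √(1545 × 0.2356) × 0.2877 − 2.394 = 3.10, so power is 0.999. With d = 0.60 × 1778 = 1067 it is 0.985. The stated 0.99 is reproduced.

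**Why the coefficient is negative.** If delay has no effect, the hazard at time t after diagnosis is λ for patients with W < t and zero for those with W ≥ t. At each early death, the patients still waiting are in the risk set, have the larger values of W and cannot die. The fitted slope on W must therefore be below zero.

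**Size, by simulation.** Assumptions: survival after treatment exponential with the medians above; W has no effect; W is gamma-distributed (shape 1 is exponential, and a higher shape means less overlap between modalities); censoring uniform over 26-230 weeks; 300 cohorts per row; about 1500-1525 deaths. The true modality hazard ratio is 0.75.

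| Mean wait in weeks, stent vs radiotherapy (shape) | Unadjusted: HR, power | With W: HR, SE, power | Delayed entry: HR, SE, power | HR for W per 4 weeks |
|---|---|---|---|---|
| 4 vs 4 (1) | 0.753, 1.00 | 0.751, 0.053, 1.00 | 0.752, 0.053, 1.00 | 0.911 |
| 2 vs 8 (1) | 0.875, 0.56 | 0.750, 0.061, 0.99 | 0.751, 0.053, 1.00 | 0.910 |
| 2 vs 8 (3) | 0.873, 0.57 | 0.746, 0.074, 0.95 | 0.749, 0.053, 1.00 | 0.903 |
| 2 vs 8 (4) | 0.874, 0.56 | 0.743, 0.079, 0.91 | 0.749, 0.053, 1.00 | 0.900 |
| 2 vs 16 (4) | 1.056, 0.06 | 0.749, 0.091, 0.82 | 0.749, 0.055, 1.00 | 0.909 |

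1. *The wait coefficient.* A hazard ratio of 0.91 per 4 weeks is 0.91³ = 0.75 per 12 weeks. It was significantly protective in most cohorts (71-100% in the main scenarios; 57% in the least affected set-up tried). It appears with equal waits too, so its direction does not depend on the unknown wait distributions. With loss to follow-up that cuts deaths to about 60%, it was 0.87-0.89 per 4 weeks. On the treatment-start clock the same covariate gave 1.00.
2. *The modality contrast.* It stays near 0.75 with W in the model and is far from it without any adjustment when waits differ. With equal true survival and differing waits, the unadjusted model rejected in 66-100% of cohorts and the model with W in 1-5.5%, against a nominal 1.67%.
3. *Precision.* Checking the second row: 0.2877/0.0607 − 2.394 = 2.35, so power is 0.99. At about 60% deaths, power with W was 0.98 for equal waits, 0.95 for 2 vs 8 (shape 1), 0.71 for 2 vs 8 (shape 4) and 0.50 for 2 vs 16 (shape 4). Delayed entry kept 0.98-1.00.

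**The case against.** The strongest reply is that W is a nuisance term put in to protect the modality contrast, and that it largely does so. The table bears this out. The article's language about delay is that of adjustment, and none of its four objectives is to estimate the effect of delay on survival. The misreading is therefore a risk, not a certainty. The same section also plans survival from treatment start, which is unaffected, and a time-varying treatment term. All of this stands. However, the time-varying term distinguishes only treated from untreated, so as worded it does not carry the three modality contrasts, and survival from treatment start is not the primary endpoint.

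A reader might also infer three stronger points that the article does not support.

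- *The stent versus radiotherapy contrast falls below its stated power.* This depends on waits by modality, which are not given. Nothing is lost with equal waits, and power is 0.99 with exponential waits of 2 versus 8 weeks. The loss comes from collinearity between wait and modality; adding W on the treatment-start clock inflates the standard error in the same way.
- *The modality hazard ratio is biased.* It is not materially so in these simulations.
- *The proportionality rule would stratify on W until strata coincide with modality.* W does tend to fail the check (92-100% of simulated cohorts), and stratifying on a quantity unknown at time zero would be undesirable. But the rule covers only important covariates. With exponential waits of 2 versus 8 weeks, stent/radiotherapy counts are about 697/150, 256/116, 129/161 and 20/249 for waits under 2, 2-4, 4-8 and over 8 weeks: three of the four strata are well mixed.

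**Conclusion.** The point holds in a limited form. The stated first remedy does not remove immortal time from the primary-clock model, and its coefficient for waiting is protective by construction: about 0.90-0.92 per 4 weeks when the truth is 1.00. The sign follows from the definition of the covariate; the size rests on assumed waits, exponential survival and the plan's medians.

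The modality hazard ratios remain close to unbiased and are much better than with no adjustment. Loss of precision is conditional. It is nil with equal waits and modest with mean waits of 2 versus 8 weeks and ordinary overlap (standard error 0.060-0.074, power 0.95-1.00). It is material only if waits are nearly separated by modality or deaths are far fewer. The reason to act is the invalid delay coefficient on the primary clock, not a general failure of power.

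**What to change.** In diagnosis-clock models of the three modality contrasts, replace the wait covariate with delayed entry: each treated patient joins the risk set at treatment start, with time still counted from diagnosis. The covariate should not simply be deleted, because the unadjusted model is much worse when waits differ. Estimate any effect of delay only in the model whose clock starts at treatment, where the wait is known at time zero, and take the modality contrasts from the delayed-entry model without the wait term.

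State that the delayed-entry contrasts describe treated patients only. The 450 patients expected to have supportive care alone have no treatment date; they are not part of the three pairwise contrasts, but any wider model that includes them needs its own rule.

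The cost is one sentence in the analysis plan and one option in the Stata or R call. No new data are needed, since the dates of diagnosis and treatment are already collected.

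### The time-varying treatment term is coded only as treated versus untreated, so it gives none of the three primary contrasts; the log-rank from diagnosis has no immortal-time correction, and the plan does not say which analysis is primary

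*Protocol article*

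**What the plan says.** The Primary endpoint section defines overall survival (OS) "as defined by time elapsed from date of diagnosis to death or last follow up". Statistical methods repeats that origin and adds a second one, "from date of initiation of treatment to date of death or the date of last patient contact". For the unadjusted comparison it says "log-rank test will be used to compare survival curves among treatments overall and stratified by the study center", without tying the test to either origin.

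The same section recognises that waits before treatment can be long and offers two measures against immortal time bias:

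- When OS runs from diagnosis, "the time from diagnosis to the initial treatment will be added as a covariate".
- When the treatments are compared with one another on OS, the section prescribes a second device: "treatment status will be included in Cox regression modeling as a time-varying covariate (defined as treated versus untreated".

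It then fixes the primary question: "Our primary analysis will examine pairwise comparisons of: stenting vs. radiotherapy with or without chemotherapy, stenting vs. chemotherapy". The third contrast is radiotherapy ± chemotherapy against chemotherapy. The Sample size section states power for these three contrasts at alpha 0.0167.

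**The concern.** The second measure is prescribed for analyses that compare treatments, yet its coding merges the treatments being compared into one state. An analyst who follows the sentence gets one hazard ratio, for any treatment against none.

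Both measures are regression devices, so neither reaches the Kaplan-Meier curves or the log-rank test. If groups are formed by the treatment eventually received and the clock starts at diagnosis, a patient must survive the wait to be counted in a modality. Each modality is then credited with its own waiting time.

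Unequal waits are plausible from Table 1. Tenwek and MNH place stents but have no external beam radiotherapy, ORCI has radiotherapy but no stents, and KCMC refers radiotherapy patients to ORCI. The bias could create a survival difference or shrink a real one. The diagnosis-based and treatment-based results could also disagree, with no rule for which governs.

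**Working it through.** **1. The stated power.** Inputs from the Sample size section: 1102 stent, 464 + 212 = 676 radiotherapy ± chemotherapy, 145 chemotherapy; medians 36, 27 and 14 weeks. Exponential survival and a two-sided test are assumed. The hazard ratios are 27/36 = 0.750, 14/36 = 0.389 and 14/27 = 0.519.

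Schoenfeld: power = Φ(√(d·p(1−p))·|ln HR| − z), with z = 2.393 for alpha 0.0167. For stent vs radiotherapy, N = 1778 and p = 1102/1778 = 0.620. With 70% events, d = 1245: √(1245 × 0.2357) × 0.2877 − 2.393 = 2.53, so power is 0.994. The stated 0.99 corresponds to about 1143 events (64%). The other two contrasts give at least 0.9998 at 70% events. The stated figures are reproduced, but they describe a direct comparison of modality groups, which the binary time-varying model does not make.

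**2. What the binary term estimates.** Write h(t) = h0(t)·exp{βZ(t) + γ'x}, with Z = 0 before any treatment and Z = 1 after. Take a stented and an irradiated patient with the same covariates, both already treated. Their hazard ratio is exp(β − β) = 1, whatever the data. With one indicator per modality it is exp(βS − βR), which is the contrast wanted.

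Simulated cohorts with the protocol's medians and group sizes agree. The binary term returned only a treated:untreated ratio of 0.84 to 0.91. The modality-specific term returned stent:radiotherapy 0.745 to 0.751 (true 0.75) and chemotherapy:radiotherapy 1.93 to 1.98 (true 1.93).

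**3. Which analysis is protected.**

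| Planned analysis | Treated vs treated | Involving supportive care |
|---|---|---|
| Log-rank/KM from diagnosis | no correction | no correction |
| Log-rank/KM from treatment start | waiting time removed | no start date |
| Cox from diagnosis + waiting-time covariate | largely corrected | covariate undefined |
| Cox, binary time-varying term | no contrast | any treatment vs none only |

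The covariate is undefined for the 450 patients forecast for supportive care alone and for anyone who dies while waiting.

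**4. Illustrative size, no true difference, stent vs radiotherapy.** All waits are assumed.

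- Simulation A: 1102 vs 676, median 30 weeks, gamma waits, censoring at 26 to 200 weeks, 400 cohorts.
- Simulation B: 1102/676/145, median 27 weeks, exponential waits, no censoring, 300 cohorts for log-rank and 40 for Cox. Deaths before treatment leave the modality group.

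The HR is radiotherapy:stent from diagnosis (for B, the inverse of the simulated 0.987, 1.076 and 1.178).

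| Mean waits (weeks) | A: HR | A: reject | B: HR | B: reject | B: reject from treatment start |
|---|---|---|---|---|---|
| 2 vs 2 | – | – | 1.01 | 2.7% | 2.7% |
| 2 vs 6 | 0.906 | 29% | 0.93 | 22% | 2.0% |
| 2 vs 8 | 0.867 | 63% | – | – | – |
| 2 vs 12 | 0.804 | 97% | 0.85 | 89% | 0.7% |

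With 300 cohorts the Monte Carlo standard error at 1.67% is √(0.0167 × 0.9833/300) = 0.74 points, so 2.7% is within noise of nominal. B is milder partly because long waiters die first: a nominal mean wait of 12 weeks becomes 1/(1/12 + ln 2/27) = 9.2 weeks among those treated.

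The chemotherapy contrasts move less. In B, with chemotherapy waits of 4 and 6 weeks, rejection was 2.7% and 5.3% against stenting, and 4.3% and 11% against radiotherapy.

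**5. Illustrative size under the protocol's medians.** In B the diagnosis-based stent:radiotherapy HR moves from 0.75 to 0.80 (2 vs 6) or 0.885 (2 vs 12), and log-rank power falls from 0.997 to 0.95 or 0.57. From treatment start, power stays at 0.997 or above.

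**6. How well the plan's own safeguards work.** In A, with no true difference, the waiting-time covariate gave HRs of 0.991 to 1.000 among treated patients, and delayed entry gave 0.997 to 1.003. A separate 30-run check at 2 vs 8 weeks gave 0.85 crude, 0.98 with the covariate and 0.99 from treatment start.

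**The case against.** The strongest reply is that the plan already holds the remedies. OS is also defined from treatment start, and nothing limits the log-rank test to the diagnosis origin, so an unbiased treated-vs-treated test is available. All three primary contrasts compare treated with treated patients, and there the waiting-time covariate works in Cox. Supportive care is in none of them. These points stand. A reader might infer that the plan cannot deliver its primary contrasts, or that it has no correction for immortal time. The document supports neither inference.

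A second reply is that the binary switch may be meant to sit beside a modality factor, or to be one switch per modality. In a small check of the first form (2 vs 8 weeks, about nine runs), the modality HR matched delayed entry (0.748 under 36 vs 27 weeks). However, the switch coefficient diverged, because patients labelled by modality cannot die before treatment, and some fits at 2 vs 12 weeks did not converge. Neither form is stated.

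A third reply is that such coding belongs in an analysis plan. That would hold had the article been silent. Instead it fixes the coding explicitly, for the very analyses where it fails, and makes diagnosis the origin of the primary endpoint.

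Finally, the waits are assumed, and so is the choice of radiotherapy as the slower modality. That stands: the size is conditional.

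**Conclusion.** The concern holds in limited form. As written, the time-varying model yields one any-treatment hazard ratio and none of the three primary contrasts. The Kaplan-Meier and log-rank comparison from diagnosis is uncorrected, and the waiting-time covariate cannot serve contrasts with supportive care. Two other planned analyses largely remove the bias among treated patients, but the plan does not name the one that carries the primary comparison.

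The 22% to 97% rejection range applies to the unadjusted diagnosis-based stent-radiotherapy comparison only. It assumes exponential survival and mean waits from 2 vs 6 to 2 vs 12 weeks. With equal waits there is no material bias. A reader might take these rates, or the power of 0.57, as the study's actual error rate or power. They are not: the protocol gives no wait by modality, and its stated power is reproduced. The ambiguity still matters, because the result depends on the analysis chosen whenever waits differ by modality.

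**What to change.** In Statistical methods:

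- Replace the binary term with a time-varying state: untreated / stent / radiotherapy ± chemotherapy / chemotherapy / esophagectomy. Each patient moves out of untreated on the date the first modality starts. Supportive-care patients and those who die waiting contribute untreated time. Take the three adjusted primary contrasts from this model.
- State that the primary log-rank and Kaplan-Meier comparisons among treated groups use the treatment-start origin already planned, or delayed entry at treatment start.
- Do not use the waiting-time covariate for any contrast that involves supportive care.

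The cost is wording and start/stop formatting of the data. Diagnosis and treatment dates are already collected (Table 3 and Chart abstraction), so no extra patients or visits are needed. The price is that supportive-care patients do not contribute to the treatment-start curves.

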### Sample size

We aim to recruit all patients with ESCC based on histological confirmation or presumptive clinical diagnosis that meet the eligibility criteria at participating AfrECC sites. We forecast a total accrual of an estimated 2476 study participants across all six sites (see Table 1) over the duration of the study. This estimate is based on annual ESCC cases observed in recent case series at KCH (unpublished data), annual recruitment to a recent case-control study at KCMC [18], as well as annual accrual rates in the present study at ORCI, MNH, and Tenwek since study initiation (Tenwek Hospital, *n* = 220 study participants per year; ORCI, *n* = 130 per year; and MNH, *n* = 150 per year). Of the total study population, we estimate 1102 study participants will be treated with esophageal stenting, 145 with chemotherapy, 464 with radiotherapy, 212 with concurrent chemoradiation, 450 with supportive care alone, and 103 with esophagectomy. Based upon previous data that indicate median OS following stenting is 36 weeks [10], radiotherapy with or without chemotherapy is 27 weeks [13, 19], and chemotherapy is 14 weeks [5, 19], our primary analysis comparing OS of different palliative interventions for ESCC will have the following power to detect differences between each pairwise comparisons based upon alpha of 0.0167 (adjusting for 3 comparisons based on Bonferroni correction): stenting vs. radiotherapy with or without chemotherapy, power = 0.99; stenting vs. chemotherapy, power = 1.00; and radiotherapy with or without chemotherapy vs. chemotherapy, power = 1.00.

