Cochran-Armitage test will be used to compare symptom metrics assessed using the ‘Modified Rosenblatt Index’ (Dysphagia, Odynophagia, ‘Chest and/or Back pain,’ WHO performance status, and ‘Overall Well-being’ since starting treatment) between each of the different palliative EC treatments (chemotherapy, radiotherapy, chemoradiation, esophageal stenting, basic supportive care) at each time point: 1 month after initiation of treatment, 3 months after the initiation of treatment and then every 3 months thereafter. We will also test for within-subject differences in scores between baseline (or pre-treatment) and each of post-treatment time points by McNemar’s Chi-squared test. In addition, generalized estimating equations (GEE) framework will be applied to analyze this longitudinal QOL data, where the treatment will be considered as the fixed effect and the subject-specific effects are the random effects.

Complications will be summarized as number of patients (%) with 95% confidence intervals and compared between treatment arms by Chi-squared test. Among palliative interventions, secondary outcome measures related to dysphagia will be compared using log-rank test and cph models to adjust covariates, including age, sex and baseline clinical covariates. ‘Time to achieve any dysphagia relief’ will be defined as time from treatment to improvement in dysphagia score of greater than or equal to 1. ‘Duration of dysphagia relief’ will be defined as time elapsed after treatment with any improvement in dysphagia from baseline. ‘Dysphagia-adjusted survival’ will be defined as the total time period with a dysphagia score of 0 to 2.

Measures of healthcare utilization and process measures related to the delivery of ESCC treatment by treatment approach will be examined as exploratory endpoints. Time-to-event measures will be compared among treatment groups by log-rank test. Count of hospitalization events, and total number of days hospitalized during and after ESCC treatment will be compared among treatment groups by ANOVA (or Kruskal Wallis test when normality assumption is not held). Chi-squared test will be used to compare the need for subsequent intervention for recurrent or persistent dysphagia by treatment approach. All analyses will be performed overall and within each site.

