## Discussions

The TOEC-Eastern Africa study will provide an overview of the therapeutic landscape of ESCC in Eastern Africa. The study will improve our understanding of the outcomes of different treatment strategies for ESCC currently in use throughout the region, including chemotherapy, radiotherapy with and without chemotherapy and esophageal stenting with SEMS. This study will address important an unmet need, as there is currently a paucity of data on the treatment of ESCC in low resource settings, particularly related to QOL [5]. The TOEC-Eastern Africa study will be the first within the region to prospectively compare treatment strategies for ESCC, and the first study in sub-Saharan Africa to evaluate QOL benefits associated with different treatments. Ultimately, findings from this study have potential to inform clinical practice guidelines for the management of ESCC in sub-Saharan Africa and other low resource settings.

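### QOL tests at each visit use only patients alive and reached, so with the planned survival differences they can reject without any QOL effect; results should be worded as conditional and shown beside a death-inclusive analysis

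*Protocol article*

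**What the plan says.** Under Statistical methods, the article tests each symptom item between the palliative treatments with a Cochran-Armitage test "at each time point: 1 month after initiation of treatment, 3 months after the initiation of treatment and then every 3 months thereafter". It then says that a "generalized estimating equations (GEE) framework will be applied to analyze this longitudinal QOL data, where the treatment will be considered as the fixed effect".

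Under Patient interviews, follow-up scores are collected by mobile phone until death or loss to follow-up. No item in Table 2 has a level for death. The article names no rule by which a dead or unreached patient enters the QOL tests.

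Under Sample size, the article plans on "median OS following stenting is 36 weeks [10], radiotherapy with or without chemotherapy is 27 weeks [13, 19], and chemotherapy is 14 weeks". The Discussions section presents the study as "the first study in sub-Saharan Africa to evaluate QOL benefits associated with different treatments".

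**The concern.** The question asked is what each treatment does for patients' QOL. The test answers a narrower one: whether score distributions are equal among those still alive and interviewed at that visit. The two differ when the groups lose patients to death at different rates and the score is related to who dies. The index includes WHO performance status and dysphagia, both of which plausibly predict death. A group with higher mortality is then reduced to its fitter members. Its remaining scores look better even if no patient's QOL was changed by treatment.

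The GEE works on the same observed scores and has no term for death, so it inherits the problem. The selection grows at later visits, where the durability of symptom relief would be judged. For overall survival the article deals explicitly with immortal time; it has no counterpart for QOL.

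**Working it through.** **Inputs from Sample size.** Medians: "median OS following stenting is 36 weeks", "radiotherapy with or without chemotherapy is 27 weeks", "chemotherapy is 14 weeks". Group sizes: "1102 study participants will be treated with esophageal stenting, 145 with chemotherapy, 464 with radiotherapy, 212 with concurrent chemoradiation". Radiotherapy with or without chemotherapy is therefore 464 + 212 = 676.

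**Reproducing the plan's own figure.** Power = Φ(|ln HR| × √(d·p·(1−p)) − z), with z = 2.39 for two-sided 0.0167. For stenting versus radiotherapy:
- HR = 27/36 = 0.75, p = 1102/1778 = 0.620, d = 1778 if all die.
- 0.2877 × √(1778 × 0.620 × 0.380) = 5.89, and Φ(5.89 − 2.39) = 0.9998.
- With follow-up assumed uniform over 6 to 53 months and 70% of the resulting events observed, power is 0.986. The article states 0.99.
- The other two contrasts give 1.00, as stated.

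The medians and group sizes are thus read as the article uses them.

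**Expected alive.** S(t) = 0.5^(t/median), exponential survival assumed:

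| Visit | Stenting | Radiotherapy ± chemotherapy | Chemotherapy |
|---|---|---|---|
| Month 1 | 92% | 90% | 81% |
| Month 3 (13 wk) | 78% | 72% | 53% |
| Month 6 (26 wk) | 61% | 51% | 28% |
| Month 9 (39 wk) | 47% | 37% | 15% |

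At month 6: 0.5^(26/36) = 0.606, 0.5^(26/27) = 0.513, 0.5^(26/14) = 0.276. That leaves about 668 of 1102, 347 of 676 and 40 of 145 patients able to give a score.

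**Rejection rate with no treatment effect on QOL.** Simulation assumptions:
- Latent frailty u ~ N(0,1), equally distributed in all groups.
- Death hazard multiplied by h per SD of u, calibrated so that each group keeps its planning median.
- Score = round(2 + 0.72u + N(0, 0.7)), limited to 0-4, higher being worse.
- 80% of survivors interviewed; linear trend test among them at month 6, two-sided 0.05.

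| Contrast | h = 1.3 | h = 1.5 | h = 2.0 |
|---|---|---|---|
| Stenting vs chemotherapy | 0.10 | 0.14 | 0.27 |
| Stenting vs radiotherapy | 0.08 | 0.09 | 0.13 |
| Radiotherapy vs chemotherapy | 0.09 | 0.11 | 0.17 |

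Repeat runs differ by a few hundredths at most. With h = 1 (health and death unlinked) the rate is about 0.05, so the selection causes the excess. A separately specified frailty model, with frailty-score correlation 0.3 to 0.7 and all survivors reached, gave 0.10-0.35 for stenting versus chemotherapy and 0.075-0.17 for stenting versus radiotherapy. At correlation 0 it stayed near 0.05.

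**Stricter alpha and early visit.** At 0.0167 the month-6 rates are about 0.05-0.14 (stenting vs chemotherapy) and 0.02-0.06 (stenting vs radiotherapy). At month 1 the rates are near nominal.

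**Direction.** In these runs nearly all rejections of stenting versus chemotherapy go against stenting. That depends on equal case mix. Keeping the planning medians but making the radiotherapy group 0.1 SD frailer at baseline reverses the sign of the mean difference from stenting. At 0.2 SD the test rejects in about 0.23-0.33 of runs, essentially none against stenting. Against chemotherapy, a 0.2-0.3 SD shift brings rejection back to about 0.04-0.08, and 0.5 SD reverses it.

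**The case against.** The other side has four good arguments.

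1. **Direction.** A reader might infer that the plan will make the longer-surviving treatment look worse. The documents do not support that as a flat statement. The cohort is not randomised, the Discussions section says that resources and access have determined treatment, and the medians come from separate earlier sources. Modest baseline differences mask or reverse the bias. This stands.

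2. **Size.** The article promises Bonferroni correction, month 1 is little affected, and the largest rates need a strong assumed link and the 145-patient chemotherapy group. This stands and limits the size. Correction lowers the rates but does not remove the bias.

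3. **Existing safeguard.** Dysphagia-adjusted survival counts time alive with a dysphagia score of 0 to 2, and overall survival is the primary endpoint. This covers dysphagia in part. Odynophagia, pain, performance status and well-being have no such measure.

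4. **Scope.** Comparing QOL among the living is a legitimate question, and handling of deaths is often left to an analysis plan. But the visit-by-visit between-treatment test and the GEE are fixed in this article, and the stated claim is about QOL benefit of treatment, not QOL among survivors.

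A stricter remedy is also tempting: allow a QOL claim only when the survivor test and a death-inclusive test agree. It should not be adopted. With a real 0.3-point benefit of radiotherapy over stenting, the survivor test rejects in about 0.96-0.99 of month-6 runs, but the agreement rule leaves about 0.04-0.08. A real 0.5-point chemotherapy benefit falls from 0.73-0.96 to 0.00. The rule would suppress real benefits of a shorter-surviving treatment.

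**Conclusion.** The point holds as a limit on what the planned QOL tests can show. By the article's own medians the groups differ markedly in who is left to be scored, and the tests can then reject without any QOL effect, at the month-6 rates shown above. The excess is large against chemotherapy and modest for stenting versus radiotherapy.

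This rests on exponential survival at the planning medians, on an assumed link between health and death, and on equal case mix for the direction. The article gives no median for supportive care, so nothing can be said about the size there. The documents do not support the stronger conclusion that the QOL results will be biased against stenting. They do support saying that a difference between treatments at a visit, in either direction, cannot by itself be read as a QOL effect of treatment.

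**What to change.** In the QOL paragraph of Statistical methods:

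- Keep the planned test at each visit, word its result as applying to patients alive and interviewed, and give the number alive and the number interviewed per group.
- Beside it, as a sensitivity analysis, report the same ordinal trend test with death before the visit scored one category below the worst level of that item (for example 5 for dysphagia, 3 for chest-back pain).
- Label the GEE estimate as conditional on being alive.
- Where the two tests point in different directions, report both and state no overall QOL benefit for either treatment. The survivor result stands as a conditional finding.

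The cost is a second run of a planned test on vital status that is already collected (Table 3). The downside is that the death-inclusive test mixes survival with QOL and does not correct confounding, so it is supportive only.
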